## Abstract

**Introduction::**

Asian countries have a variety of ethnic groups and culture that provide their own traditional treatment in health care. Facial candling appears to be one of the popular traditional treatments in Southeast Asian. The complementary medicine practitioners promote that the facial candling treatment would help in reducing the symptoms of allergic rhinitis and other problems related to sinus. Due to the lack of evidence available, the effectiveness of this treatment method and its mechanism, however, remains unknown. The objective of this research is therefore to study impact of facial candling on inflammatory mediators, substance P (SP), symptoms severity, and quality of life (QoL) in allergic rhinitis patients.

**Method and analysis::**

A randomized, nonblinded, controlled trial will be carried out by recruiting a total of 66 eligible allergic rhinitis patients who fulfill the inclusion criteria from a university health center. The subjects will be randomly assigned into 2 groups: intervention group receiving facial candling treatment and control group (no treatment given). Samples of blood and nasal mucus will be collected right before and after intervention. Samples collected will be analyzed. The primary outcomes are the changes in the level of SP in both blood and mucus samples between both groups. The secondary outcomes include the levels of inflammatory mediators (ie, tumor necrosis factor alpha, interleukin (IL)-3, IL-5, IL-6, IL-10, and IL-13) and the severity of allergic rhinitis symptoms as measured by a visual analogous scale and QoL using the Rhinitis Quality of Life Questionnaire (RQLQ).

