### Outcome measures

2.4

The primary outcome measure for this study is the difference in the level of SP in blood and nasal mucus samples in pre- and postintervention. The secondary outcome measures include the levels of inflammatory mediators (tumor necrosis factor alpha [TNF-α], IL-3, IL-5, IL-6, IL-10, and IL-13) in both blood and nasal mucus samples. Other secondary outcome measures also include the visual analogous scale (VAS) score (indicating the pain intensity) and the Rhinitis Quality of Life Questionnaire (RQLQ).

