### Sample size calculation

2.6

The sample size is calculated using Power and Sample Size software 3.1.2 version. The difference between the mean values of the intervention and control groups, and the standard deviation (postmassage) of SP levels^[27]^ will be used as parameters for sample size calculation given there is no previous finding of the immediate effect of facial candling treatment on SP. The mean levels of SP in the intervention group and control group are 50.43 and 56.27 pg/mL, respectively (the difference in the mean values between the experimental and control groups is 5.84 pg/mL).^[27]^ The type I error probability associated with this test of the null hypothesis is 0.05. A sample of 33 experimental subjects and 33 control subjects is therefore required to reject the null hypothesis that the population means of the experimental and control groups are equal, with a probability (power) of 0.8.

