### Data analysis plan

2.7

Data will be analyzed using SPSS software version 20.0. Mean, standard deviation, and range will be calculated for each variable. Data will be tested for normality; paired *t* test will be used (if the distribution is normal) or Mann–Whitney (if the distribution is skewed) to measure the differences pre- and postintervention within and between groups for every outcome measure. A *P* value of less than 0.05 will be used to show that the result is statistically significant.

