## Discussion

3

There is growing awareness that the knowledge of SP may help to develop new methods to treat pain and inflammation.^[19,28,29]^ For example, SP and inflammatory mediators appear to play a role in allergic rhinitis.^[30,31]^ Recently, the role of SP in the pathophysiology of clinical syndromes such as inflammatory rhinitis and diseases with chronic inflammatory pain in general is becoming clearer.^[32]^ It can be expected that the development of drugs and interventions aimed at the modulation of SP will be able to help in treatment of pain associated with these diseases. Previous study used the level of SP in nasal mucus to indicate the severity of pain in many chronic pain conditions, because the amount of SP is significantly greater in nose mucus than in plasma.^[33]^

As there is no previous finding related to facial candling, we explored studies that trialed effectiveness of other complimentary treatment methods. For example, 23 patients (19 were serologically tested positive for allergic diseases) with persistent allergic rhinitis were treated with 4 acupoint herbal plaster applied using the moxibustion technique. Clinical outcomes measured using the RQLQ indicated that the patients tested positively for allergic disease responded better to the treatment. Furthermore, IL-13 immune response was downregulated in that particular group of patients.^[22]^ Similarly, another study demonstrated the effectiveness of subcutaneous injectable immunotherapy in treating the sinus inflammation and pain in 281 allergic rhinitis patients. The subcutaneous immunotherapy as treatment of allergic rhinitis led to a reduction in all symptoms studied, improving the QoL of patients.^[34]^ Antiinflammatory effects of acupuncture and their relevance to allergic rhinitis have also been examined.^[35]^ Acupuncture has been shown to significantly reduce histamine-induced symptoms of allergic rhinitis. Furthermore, the study showed that there is significantly reduce of IL-4 and IL-10 in allergic rhinitis patients as acupuncture treatment has been applied^[36]^ and their finding was supported by Petti et al,^[37]^ who revealed the significant decrease of IL-10 immediately after acupuncture treatment. Interestingly, they showed unpredicted significant decrease of IL-2 and no significant changed in IL-6.

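### Blood SP and nasal-mucus SP are both primary, each judged at P<0.05, but the stated 0.05 type I error and 0.8 power are for one SP comparison; for the trial, one of the two figures fails

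*Protocol article*

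**What the plan says.** The abstract (Method and analysis) uses the plural: "The primary outcomes are the changes in the level of SP in both blood and mucus samples between both groups". Section 2.4 (Outcome measures) names both fluids again and gives neither the lead: "The primary outcome measure for this study is the difference in the level of SP in blood and nasal mucus samples".

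Section 2.7 (Data analysis plan) applies its tests "to measure the differences pre- and postintervention within and between groups for every outcome measure", and a P "value of less than 0.05 will be used to show that the result is statistically significant". It sets one threshold, with no split and no order of testing.

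Section 2.6 (Sample size calculation) is written for one test: "The type I error probability associated with this test of the null hypothesis is 0.05". It uses one effect, "the difference in the mean values between the experimental and control groups is 5.84 pg/mL", and "the standard deviation (postmassage) of SP levels" from a cited study. The SD is not printed, sidedness is not stated, and the fluid is not named. The result is 33 per group with power 0.8.

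**The concern.** With two primary results there are four possible outcomes, and the plan does not say how to read the two split ones (one fluid significant, the other not). Whichever reading is adopted, one of the two figures in section 2.6 stops describing the trial:

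- If either fluid suffices, there are two chances of a false positive at 0.05 each, and the error for the primary claim exceeds 0.05.
- If both fluids are needed, the error stays at or below 0.05, but two tests have to succeed and power is below 0.8.

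A split result could also be called a success or a failure after the data have been seen. The trial is nonblinded, and section 3.1 expects its results to support prescribing the treatment, so the error rate behind the primary claim should be the one stated.

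**Working it through.** **Inputs from the protocol article.** Section 2.6: means 50.43 and 56.27 pg/mL, difference 56.27 − 50.43 = 5.84 pg/mL; alpha 0.05; power 0.8; 33 per group. Section 2.7: threshold 0.05 for each outcome. Abstract and section 2.4: two primary outcomes.

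**Assumptions, because the article gives no figure.** Tests are two-sided. The correlation ρ between the blood and mucus test statistics runs from 0 to 0.9. For joint power, the standardized effect is the same in both fluids, and each fluid alone has 80% power.

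**Step 1: the plan's own figure.** The SD is not printed, so 33 per group cannot be reproduced independently. Solving backwards for the SD that gives power 0.8 with 33 per group:

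- Normal approximation: d = (1.960 + 0.842) / √(33/2) = 2.802 / 4.062 = 0.690, so SD = 5.84 / 0.690 ≈ 8.47 pg/mL.
- Noncentral t: d ≈ 0.70, so SD ≈ 8.34 pg/mL.

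The 33 per group is therefore consistent with one comparison at d of about 0.70. It leaves no allowance for a second primary test.

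**Step 2: either fluid suffices.** For independent tests, familywise error = 1 − (1 − 0.05)² = 1 − 0.9025 = 0.0975. For ρ > 0, it is 1 − P(|Z₁| < 1.96 and |Z₂| < 1.96) under a bivariate normal with correlation ρ.

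**Step 3: both fluids required.** For independent tests, joint power = 0.8 × 0.8 = 0.64. For ρ > 0, it is P(Z₁ > 1.96 and Z₂ > 1.96) with both means at 1.960 + 0.842 = 2.802.

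| ρ (assumed) | Error, either suffices | Power, both required |
|---|---|---|
| 0 | 0.0975 | 0.640 |
| 0.3 | 0.0951 | 0.666 |
| 0.5 | 0.0907 | 0.687 |
| 0.7 | 0.0835 | 0.713 |
| 0.8 | 0.0781 | 0.729 |
| 0.9 | 0.0704 | 0.750 |

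The two stated figures hold together only at ρ = 1. The error column covers only the two between-group SP tests. Section 2.7 also plans within-group tests, which are not counted here.

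**Step 4: what each remedy does to power at 33 per group.**

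- *One primary, fixed sequence.* The first test keeps 0.05 and 0.8, provided the 5.84 pg/mL and its SD apply to that fluid. The second fluid is declared significant only if both tests succeed, so its power is the last column above.
- *Bonferroni, or the first step of Holm (0.025).* Power is 0.708 by noncentral t at d = 0.70 and 0.712 by the normal approximation, so about 71%.
- *Holm.* A fluid is significant if its P ≤ 0.025, or if its P ≤ 0.05 and the other fluid's P ≤ 0.025. With equal effects, power per fluid is 0.775 (ρ = 0), 0.765 (ρ = 0.5) and 0.751 (ρ = 0.9), so about 75 to 78%. The 71% is therefore a first-step figure and not the per-fluid power under Holm.

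**The case against.** **A separate analysis plan may hold the decision rule.** This is fair as far as the missing rule goes; a condensed article may leave that out. But the article itself fixes 0.05 for every outcome and a sample size for one test. Any later rule would have to change the threshold in 2.7 or make the power in 2.6 untrue, so the printed text needs correcting either way.

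**The wording permits a both-fluids reading.** The abstract says both samples, and 2.4 uses the singular for the primary outcome. On that reading the type I error is not inflated. This stands, and it is why the point is an either-or; power then falls short of 0.8.

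**A reader might infer that the false-positive rate is simply doubled.** The documents do not support that. The 9.75% needs independent tests and the either-fluid rule, and the correlation is not given. At ρ = 0.9 the figure is 7.0%.

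**A reader might infer that mucus SP is the natural single primary.** The Discussion notes that mucus SP has been used "because the amount of SP is significantly greater in nose mucus than in plasma", in the setting of chronic pain. That describes the amount of SP and does not show that the difference and SD in 2.6 apply to mucus. If mucus levels are higher, those values may not transfer. The documents do not settle the choice.

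**A reader might also infer that the other outcomes are treated as confirmatory.** The mediators, VAS and RQLQ are already labelled secondary in the abstract and 2.4, so the point is confined to the two SP outcomes.

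**Conclusion.** The point holds as a conflict within the protocol article. Two primary outcomes, a 0.05 threshold for each, and a sample size for one test cannot all stand with both stated figures. For any between-fluid correlation below 1, one of these applies:

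- familywise error of about 7 to 10% in place of 5%, if either fluid suffices;
- power of about 64 to 75% in place of 80%, if both are required.

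The ranges rest on an assumed correlation of 0.9 down to 0 and two-sided tests. The power range also assumes equal standardized effects with 80% power in each fluid alone. The back-solved d of about 0.70 affects only the Bonferroni and Holm figures. These assumptions set the size of the gap, not its existence.

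**What to change.** Before any outcome data are analysed, and by a dated amendment with reasons (the abstract reports registration and a first enrolment), choose one of the following:

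1. **Preferred: one primary.** Name one fluid as the single primary, preferably the one to which the 5.84 pg/mL and its SD in 2.6 apply, and state that fluid in 2.6. Test the other only if the first is significant, each at 0.05. This keeps 0.05, 0.8 and 66 patients, provided the planning values belong to the chosen fluid.
2. **Both primary, Holm at 0.05 overall.** Restate power in 2.6: about 71% at the first-step alpha of 0.025, and about 75 to 78% per fluid if both effects are equal. Declare that these rest on d of about 0.70, back-solved from 33 per group.
3. **Both required, each at 0.05.** State that rule and give joint power as about 64 to 75%, with its assumptions.

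Change the abstract, 2.4, 2.6 and 2.7 to match, so that 2.7 no longer applies a bare 0.05 to both primaries without a rule.

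Cost: one fluid loses stand-alone primary status (option 1), or the stated power becomes less favourable (options 2 and 3). No extra patients are needed if that is accepted.

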**Ethical and trial registration::**

The study protocols are approved from the Ethical and Research Committee of the Universiti Teknologi MARA (REC/113/15). The trial is registered under the Australia New Zealand Clinical Trial Registry (ACTRN12616000299404). The trial was registered on 03/07/2016 and the first patient was enrolled on 10/12/2016.

**Conclusion::**

Facial candling is one of the unique treatments using candles to reduce the severity of symptoms and inflammation. This is the first ever study conducted on facial candling that will give rise to new knowledge underlying the effects of facial candling on severity of symptoms and inflammation relief mechanism mediated by substance P and inflammatory mediators.

## Introduction

1

In local Indonesian and Malaysian languages, allergic rhinitis is known as resdung. It is characterized by nasal symptoms that include posterior or interior rhinorrhea, nasal blocking, sneezing, and/or nose itchiness which present for more than 2 consecutive days with a minimum of 2 hours each day.^[1]^ Allergic rhinitis is a common disease globally including in the region of Asia.^[2]^ Several prevalence studies have shown that the annual prevalence ranged from 15.1% to 37.8% whereas the lifetime prevalence of allergic rhinitis ranged from 18.3% to 47.7% in the United Kingdom and Netherland population.^[3]^ Similarly, annual prevalence is 7.8% among adults in the United States (US) adults and 10% to 30% worldwide.^[4]^

Allergic rhinitis can cause serious implications to the mental health and physical status as it impairs quality of life (QoL), sleep, work, and school.^[5]^ Besides that, it significantly gives an impact on the expenses of health care. For instance the annual total direct and indirect costs of allergic rhinitis were approximately US dollar 2.7 billion and US dollar 1.4 billion in US and Sweden, respectively.^[6,7]^

Allergic rhinitis, one type of atopic syndromes, is a predisposition toward an exaggerated immunoglobulin E (IgE) mediated immune response in reaction to an environmental allergen such as food and allergen.^[8]^ Two main pathophysiologic mechanisms have been proposed. According to the first approach, in early phase of inflammation, the allergen activated B cell to produce IgE antibody.^[9]^ The IgE antibody then occupies the surface of mast cell which subsequently releases prostaglandin, histamine, and other chemical mediators into surrounding tissues. The release of mediators will then increase vascular permeability, vasodilatation, and increase mucus production,^[10]^ resulting in itching, sneezing, and congestion.^[11]^ Further release of inflammatory mediators promote a late-phase reaction which encourages the production of inflammatory mediators and hence, triggering the activation that causes the nasal mucosa cells to be assembled.^[12]^ The second approach suggests that allergic rhinitis is caused by an imbalanced T helper (Th)1 and Th2 cell-mediated response.^[13,14]^ Allergic rhinitis patients exhibit IgE, mast cell, and Th2 lymphocyte immune responses related to the early phase (symptoms: sneezing, nasal itching, runny, and congested nasal passages) as well as the late phase of the disease (symptoms: patient fatigue, malaise, and irritability).^[15]^ Th1 cells primarily secrete interleukin (IL)-2 and IL-3; whereas Th2 cells secrete IL-3, IL-4, IL-5, IL-10, and IL-13.^[16]^ Dominant Th2 cytokines can enhance allergen-specific IgE, which plays an important role in allergic inflammation.^[13,15]^

Previous study has shown that substance P (SP) involves in transference of noxious stimuli located in the spinal cord.^[17]^ SP is increasingly being recognized to play an important role in the inception of allergy and inflammation.^[18,19]^ In this case, SP increases immunoglobulin production, lymphocyte proliferation, and enhances cytokine secretion from monocytes, lymphocytes, macrophages, and mast cells. Apart from that, the release of inflammatory mediators including cytokines, histamine potentiates tissue injury, and stimulates further leukocyte recruitment, subsequently increase the inflammatory response.^[20]^

Most of the Asian countries are multiracial and cultural whom each community has specific method of traditional treatment.^[21]^ Facial candling, also known as *lilin resdung*, is one the traditional treatments used by the Indonesian and Malay ethnicities groups to cure or reduce various allergy and inflammation conditions including allergic rhinitis. In other Asian countries such as China and Japan, facial candling is practised in the form of moxibustion where burning cigar-shaped dried mugwort stick is used to warm regions and meridian points.^[22]^ Facial candling treatments are believed to give various impacts to the patients, including reducing stress as it promotes relaxation, and reduces headache, ear, or throat infection.^[23]^ Furthermore, the facial candling technique is said to improve the blood circulation throughout the whole body and reduce symptoms of allergic rhinitis. Usually after the facial candling treatment, there is white like powder left on the face of the clients which the practitioners insist that the white like powder is the evidence of fat eliminated during the process.^[24]^ However, there is a paucity of scientific evidence to support the execution of facial candling and the concept on how the treatment reduce and exert its effect on allergy and inflammation. There could be a link between the immediate effect of facial candling that could reduce the SP and inflammatory mediators in affected patients. It is also crucial to investigate the immediate effect of facial candling on symptoms severity and QoL on allergic rhinitis patients. Findings from this research will be instrumental to elucidate the value of facial candling on human pathological process.

## Method and analysis

2

### Study design and patient recruitment

2.1

A randomized, nonblinded, controlled trial will be carried out at a health clinic located at Universiti Teknologi MARA (UiTM), Puncak Alam, Malaysia. A total of 66 allergic rhinitis patients who have seen ear–nose–throat specialist at a university health clinic and fulfill the inclusion criteria will be invited to participate in this study. Skin prick and puncture test (SPT) was performed to confirm the diagnosis before enrolment confirmation by otolaryngologists to exclude patients with sinusitis and nasal polyps.

An otorhinolaryngology specialist will conduct confirmatory medical examination for the subjects and screening based on inclusion and exclusion criteria. The inclusion criteria are as follow: has a positive skin prick test, age between 18 and 65 years old, and negative urine pregnancy test for female. The participants will be excluded if they are diagnosed with chronic obstructive pulmonary disease, sinusitis/rhinosinusitis, nasal polyps, asthma, taking medication containing analgesic, antihistamine and steroid, and pregnant.

An explanatory statement will be given and writing informed consent will be obtained prior to the commencement of the study. The participant will then be randomly assigned into 2 groups: allergic rhinitis patients or control groups (Fig. 1). Patients will be asked to choose among the sequentially numbered, sealed envelopes containing the group allocation, which will be determined by a computer-generated random number. An independent researcher produces the random numbers and prepares the envelopes. The current study is funded by UiTM and Ministry of Higher Education of Malaysia. Ethical approval has been obtained from the UiTM Research Ethics Committee (REC/113/115). The trial is registered under Australia New Zealand Clinical Trial Registry (ACTRN12616000299404).

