### Interventions

2.2

The facial candling treatment will be conducted for 15 minutes by a certified practitioner using a plain unscented facial candle. The facial candle is made of cloths which are soaked in beeswax. The facial candle is 9 to 10 inches in length and 0.25 to 0.5 inches in diameter. First, the patients will lie down on a massage table bed. Then, their both eyes will be closed with cotton to prevent the ash of the candle irritated the eyes during the treatment. Next, the candle will be kept in a vertically upright position and the large end of the candle is lit. After that, smoke that released by the candle will be passed around the patients face. Last, the face will be cleansed with water. Meanwhile, the control group will lie in a relaxation positions within 15 minutes prior assessment (no facial candling treatment) (Fig. 1).

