### Blood and mucus collection

2.3

Before and after the facial candling treatment, about 10 mL of venous blood will be taken by a certified phlebotomist. The whole blood will be collected into plain polyethylene tube until blood clot formation. After that, clots are separated from the wall of tube using a wooden applicator stick. Approximately 3 mL of nasal mucus will be collected with a suction from an aided vacuum that does not require chemical stimulation to prevent the introduction foreign substances into the nasal fluids. A small rubber-tipped vacuum device will be inserted gently inside the nasal passageways to stimulate nasal secretions. Both blood and nasal mucus samples will be collected and centrifuged (10,000 g and 4 °C for 15 minutes) to eliminate debris and cellular matter. The supernatant will be stored at −80 °C until analysis.

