### Instruments

2.5

All samples will be analyzed individually using commercial human enzyme-linked immunosorbent assay kits (Table 1). The VAS is a measurement of pain and symptom intensity and has been found to be acceptable to patients and valid.^[25,26]^ The scale ranges is from “0” to “10” with a different facial expression whereby 0 represents “no pain/symptom” and 10 represents the “worst possible pain/symptom.” In this study, patients will be asked to rate their pain and symptom severity using the VAS pre- and postintervention. RQLQ will also be used to assess the disease-associated problems of the participants in 7 aspects of daily life: activities, sleep, nonnose/eye symptoms, practical problems, nasal symptoms, nose symptoms, and emotional symptoms. The score of each of the item is graded into 0 to 6. The total score of the 7 items will be calculated for every participant at baseline (1 day before) and 1 day after the intervention.

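### The trial is labelled nonblinded with no exception for the laboratory, although its primary outcome is an assay on frozen samples that can be masked

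*Protocol article*

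**What the plan says.** The blinding status is given twice. The abstract (Method and analysis) says: "A randomized, nonblinded, controlled trial will be carried out by recruiting a total of 66 eligible allergic rhinitis patients". Section 2.1 (Study design and patient recruitment) says: "A randomized, nonblinded, controlled trial will be carried out at a health clinic". Neither sentence limits the label to particular people, and no passage shown describes masked staff or coded samples.

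The primary outcome is set in section 2.4 (Outcome measures): "The primary outcome measure for this study is the difference in the level of SP in blood and nasal mucus samples in pre- and postintervention". Cytokines (TNF-α and five interleukins) are secondary outcomes in the same two fluids. Section 2.5 (Instruments) gives the method: "All samples will be analyzed individually using commercial human enzyme-linked immunosorbent assay kits". Section 2.3 (Blood and mucus collection) separates sampling from assay: "The supernatant will be stored at −80 °C until analysis".

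Two further points bear on what can be masked. Under section 2.2 (Interventions) the control arm only rests, with no sham candling. Section 2.1 already involves someone apart from the study team in the allocation: "An independent researcher produces the random numbers and prepares the envelopes".

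**The concern.** An open design is unavoidable for the patient and the practitioner. It is not unavoidable for the person who runs the assay, who works later on a stored tube and needs to know neither the arm nor whether the sample was taken before or after the session.

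An ELISA is read by an instrument, but people still decide which wells to repeat, which dilution to use and which values to discard. If they know the arm, those choices can differ between arms. If they know the time point, the choices can affect the within-group comparisons before and after the session, which section 2.7 plans alongside the between-group ones. The Discussion and section 3.1 express a clear expectation that candling reduces SP and allergy, and masking guards against the effect of such an expectation.

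The symptom scale (VAS) is rated by patients who know their arm, and the RQLQ is a questionnaire on their own problems, so neither can be protected in this design. SP and the cytokines can be. That makes the unqualified label matter most for the primary outcome.

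**Working it through.** **Step 1: who can be masked, according to the article**

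| Role or outcome | What the article fixes | Can it be masked? |
|---|---|---|
| Patient | Candling or rest, no sham (2.2) | No |
| Practitioner | Performs the candling (2.2) | No |
| VAS, RQLQ | Patient's own ratings (2.5) | No, the patient knows the arm |
| SP (primary), cytokines | ELISA (2.5) on frozen supernatant (2.3) | Yes, by coding the tubes |
| Stated status | Nonblinded, without qualification (abstract, 2.1) | Does not make this distinction |

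The last two rows do not fit together. The stated status covers the one group of outcomes for which an open design is not needed.

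**Step 2: the plan's own sample size figure**

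Inputs from section 2.6: SP means 50.43 and 56.27 pg/mL, alpha 0.05, power 0.8, 33 per arm. The difference checks: 56.27 − 50.43 = 5.84 pg/mL. Neither the SD nor the sidedness of the test is printed, so 33 per arm cannot be reproduced directly. The SD that gives it can be solved for:

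- Two-sided test, noncentral t: standardized difference 0.700, so SD = 5.84 / 0.700 ≈ 8.34 pg/mL. The normal approximation gives 8.47.
- One-sided test, noncentral t: SD ≈ 9.44 pg/mL.

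Nothing in this calculation depends on blinding. Masking the assay changes neither the sample size, nor alpha, nor nominal power.

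**Step 3: sensitivity to an assumed reading shift (illustration only)**

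Assume the two-sided SD of 8.34 pg/mL. The standard error of the difference between arms is

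SE = SD × √(2/n) = 8.34 × √(2/33) ≈ 2.05 pg/mL.

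Suppose there is no true effect, but handling of the assay moves one arm by b relative to the other. By the normal approximation,

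rejection rate = 1 − Φ(1.96 − b/SE) + Φ(−1.96 − b/SE).

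For b = 2: b/SE = 2/2.05 ≈ 0.97, and the rate is about 0.16.

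| Assumed shift b (pg/mL) | Share of control mean (56.27) | Type I error, normal | Type I error, noncentral t |
|---|---|---|---|
| 0 | 0% | 0.05 | 0.05 |
| 1 | 1.8% | 0.08 | 0.077 |
| 2 | 3.6% | 0.16 | 0.160 |
| 3 | 5.3% | 0.31 | 0.302 |

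A shift of 2 pg/mL is about a third of the planned difference (2 / 5.84 = 0.34) and roughly triples the false-positive rate. The shift has to differ between arms. An error common to both arms cancels in the between-group comparison.

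**The case against.** The strongest case on the other side is that this is mostly silence. The word nonblinded describes the design and fits a control without sham. It may be meant only for patients and practitioner. No passage says that assay staff know the arm, that tubes carry the allocation, or that the treating team runs the ELISA. A condensed article may leave sample coding and rules for repeats to a full protocol or laboratory manual, and Table 1 and Figure 1 are not shown. ELISA is also less open to observer influence than a patient's rating.

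Most of this stands, and it limits the point. A reader might infer that the whole trial, laboratory included, is run unmasked; the documents do not establish that. What remains is that the article states a blinding status twice, without qualification, and that status is weaker than its primary outcome permits. That is more than an omitted detail.

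A reader might also blame the open label for plate effects. With 66 × 2 = 132 samples per fluid, several plates would be needed if the kits use 96 wells (an assumption). But confounding with plate comes from how samples are laid out, not from who is masked. Masking would not remove it, and an unmasked reader does not create it. The article fixes no layout, and its silence there is not a fault.

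Finally, the error rates above might be taken as expected inflation. They are not: the shifts are assumed, and the SD is back-solved for a two-sided test that the article does not state.

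**Conclusion.** The point holds as a design choice that can be improved. The article labels the trial nonblinded with no exception for the laboratory, while SP and the cytokines are measured on stored samples and could be assessed blind. It is worth correcting because it concerns the primary outcome in a trial whose patient-rated outcomes are necessarily open.

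No figure in the article is shown to be wrong, and no bias is shown to occur. The size given, a type I error of about 0.16 for a 2 pg/mL shift, rests on three assumptions: a two-sided test, an SD of about 8.3 pg/mL, and the shift itself. It shows how sensitive the comparison would be and predicts nothing. If the laboratory is in fact masked, stating so in the text resolves the point.

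**What to change.** Reword sections 2.1 and 2.5, and the matching label in the abstract, to say that the trial is open to patients and practitioner with blinded laboratory assessment. Specify that:

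- each tube carries a code that shows neither arm nor time point;
- the key is held by someone outside the laboratory, for example the independent researcher who prepares the envelopes (a new task, since section 2.1 gives that person only the random numbers and envelopes);
- repeats and exclusions of assay values are settled before the key is opened.

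Optional good practice, separate from blinding: run a patient's samples from before and after the session on the same plate, with both arms mixed on each plate. If this is adopted, the code must let the plate map pair the samples without revealing their order.

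The cost is small: labelling, a held key and a few sentences. No extra samples or assays are needed, and the sample size, alpha and clinical procedures do not change. Because the supernatant is stored before analysis, samples already collected could still be recoded by someone outside the laboratory before they are assayed.
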